#### Self-Efficacy

The Self-Efficacy for Managing Chronic Disease Scale [54] was developed to measure self-efficacy in people with chronic conditions. It has been previously used in a cancer patient population, and has also been adapted to assess cancer-specific self-management behaviors. We will therefore be using the adapted Cancer Survivors Self-Efficacy Scale for this research [49]. Patients will rate their confidence to perform 6 self-management behaviors on a scale of 1 to 10. A mean score will then be calculated, with a higher value indicating greater self-efficacy. Previous investigations into prostate cancer survivor self-efficacy have been positive; patients reported being generally confident with their ability to keep their symptoms or health problems from interfering with their lives. In relation to cancer specifically, patients were also generally confident they could access information and support, deal with problems the cancer may have caused, and contact their clinicians with any problems. We are interested in exploring whether our patient population will share a similar self-efficacy status.

#### Prostate Cancer-Related Level of Anxiety

We will assess the psychological difficulties faced by prostate cancer survivors using the Memorial Anxiety Scale for Prostate Cancer (MAX-CP) [56], which has been validated to measure anxiety in men with prostate cancer receiving ambulatory care. This 18-item scale consists of 3 subscales measuring anxiety related to prostate cancer, fear of recurrence, and PSA-related anxiety. In the original validation study, it was anticipated that patients with rising PSA levels would display more PSA-related anxiety; however, this hypothesis received only limited support and correlated modestly with changes in MAX-CP scores. We would like to further explore this correlation in our own patient population to better understand the sensitivity of PSA-related changes to anxiety status.

#### Patient Experience of Ned

In addition to exploring the acceptability of Ned by patients, we will also ask them about their experience using the app to capture emerging themes of how it translates into a real-world setting. We will conduct semistructured interviews with 20 patients at study conclusion, alongside a qualitative observation session where we will ask patients to perform a series of tasks in Ned while observed by an evaluator. The contents of this interview will be modeled after the Greenhalgh interview framework [41] (Multimedia Appendix 2). This will help us to determine the design-translation gap and improve the app’s workflow. The research team will recruit interviewees through snowball sampling all patients who complete their 12-month study assessment and consent to being interviewed. This will mean that patients who are enrolled earlier will have a greater chance of being interviewed poststudy about their experience with Ned. Our justification for this decision is proactive in nature: we want to understand how patients experience Ned as early as possible so that we can address any reported concerns or difficulties with the app and improve it for the remaining participants in the study. This will ultimately ensure that the least number of patients possible will be exposed to an unfavorable version of Ned.

#### Caregiver Experience of Ned

The experience of prostate cancer survivorship is often a shared one, with the caregivers of survivors taking on the responsibility of advocating for greater survivorship care [57]. Caregivers should be fully integrated into the circle of care and have access to the same information as patients do if they are expected to effectively advocate on their behalf. We believe that for Ned to have a meaningful impact on the survivorship experience, the app must enable caregivers to easily access their partner’s health data to create a full record of care. Ned must also be a seamless and facilitating addition to the tasks of care. As caregivers advocate for their partners’ health needs, a fluid transfer of data between patient, caregiver, and clinician that can be referenced and acted upon during point-of-care interactions may help to improve overall survivorship care. With Ned as a resource, caregivers may be able to prevent the loss of laboratory results and gain the opportunity for evidence-based discussions of symptoms where clinical interactions are not subject to recall bias and nerves. We will explore how caregivers perceive using Ned to support their partners through conducting a semistructured interview with 10 caregivers, the contents of which will be modeled after the Greenhalgh interview framework [41] and the modified EPIC-Partner framework [8,57] (Multimedia Appendix 3).

#### Clinician Experience of Ned

Future scalability and sustainability efforts for Ned will depend on how clinicians perceive the app and their willingness to champion its use in hospitals and homes. We will use the Canada Health Infoway System and Use Assessment Survey to assess clinician adoption, use, and satisfaction with Ned alongside information and system quality [58]. We have modified the original survey to elicit Ned *-* specific insights and will be delivering the survey to 10 clinicians as a Web-based questionnaire to maximize convenience and ease of survey completion.

### Sample Size

The appropriate sample size for single-case research depends on the specific research question being investigated and cannot be calculated in the same way as group designs such as the randomized controlled trial. In his seminal writing on case study designs, Yin recommends abandoning traditional sampling logic in favor of reflecting on the number of replications that are desired to maximize both certainty of research findings and external validity [59]. However, we recognize that our study design diverges from traditional case study methodology in nesting a within-group pre-post comparison of health outcomes aimed at identifying possible parameters of clinical change from baseline to study conclusion. We have therefore diverged from Yin’s recommendations and performed a sample size calculation powered to detect a minimal clinically important difference (MCID) of 4 with a standard deviation of 22.25 on the EPIC-26. We selected the most conservative MCID and the median standard deviation from the range of validated values (MCID range 4-12, SD range 12.6-31.9), which have been widely used in prostate cancer survivorship research [60]. With 90% power, an effect size of Cohen *d*=0.16, and a 2-sided significance level of 5%, a minimum of 317 participants are required to detect this MCID. We anticipate a dropout rate of 20%, bringing our total sample size to 400 prostate cancer survivors for recruitment. We performed this calculation using the G*Power 3.1 software [61]. We will actively recruit the 400 patients required to power our within-group pre-post comparison of health outcomes, but we do not have a predetermined sample size for caregivers and clinicians. We anticipate that 10 clinicians will accept the invitation to join the Ned study and 50% of patients will share Ned with their caregivers. This will result in a total study sample size of 610 participants, composed of 400 patients, 200 caregivers, and 10 clinicians.

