#### Health-Related Quality of Life

We will assess prostate cancer-specific quality of life and functional recovery after treatment using the EPIC-26 [39]. The EPIC-26 is a reliable and valid scale with 26 items assessing 5 health domains: urinary continence, urinary irritation, sexual function, bowel function, and hormonal expression. It is scored on a summary scale from 0 to 100, with higher scores corresponding to higher health states. We will also use the Prostate Cancer-Related Quality of Life Scales [51] to complement the EPIC-26, as the scales are designed with a stronger focus on patient perception and derived meaning from treatment outcomes. Each individual scale contains between 2 and 8 items and is rated on a 5-point Likert scale. We will specifically be using the following 6 scales: Health Worry, PSA Concern, Cancer Control, Informed Decision, Regret, and Outlook.

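### The sample-size paragraph prints Cohen d = 0.16, but its own difference of 4 and SD of 22.25 give d = 0.18; the printed d, 317 completers and 90% power cannot all hold

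*Protocol article*

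**What the plan says.** All the planning figures stand in one paragraph of the protocol article, Methods, Sample Size.

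- The calculation is "powered to detect a minimal clinically important difference (MCID) of 4 with a standard deviation of 22.25 on the EPIC-26".
- The source of these values is given as "the median standard deviation from the range of validated values (MCID range 4-12, SD range 12.6-31.9"; the MCID is the lowest in its range.
- The standardised effect is printed as "an effect size of Cohen *d*=0.16", with 90% power.
- The conclusion is "and a 2-sided significance level of 5%, a minimum of 317 participants are required to detect this MCID". With 20% dropout this becomes 400 recruited, computed in G*Power 3.1.
- The 400 patients are described as "required to power our within-group pre-post comparison of health outcomes", so the comparison is within patient. The section describes it as change from baseline to the end of the study. The Trial Design section and Table 2 put that at 12 months.

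The Health-Related Quality of Life section describes the instrument as having "26 items assessing 5 health domains: urinary continence, urinary irritation, sexual function, bowel function, and hormonal expression". The Sample Size section does not say which domain the 4 points refer to, whether 22.25 is the SD of a score or of a change, or what pre-post correlation is assumed.

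**The concern.** The standardised effect in a paired calculation is the difference divided by the SD of change. The paragraph gives the difference, an SD and the standardised effect, and the third does not follow from the first two. A reader who starts from d = 0.16 and a reader who starts from 4/22.25 reach required numbers that differ by 85 completers (413 against 328), and neither reaches 317 with a paired test.

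This is the only power statement in the article, and it justifies recruiting 400 patients. If 12-month EPIC-26 change turns out non-significant, the result will be read against the 90% figure. That is close to right for a 4-point change with an SD of change of 22.25, and about 9 points too high for an effect of d = 0.16. The paragraph should let the reader see which one was planned.

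**Working it through.** **Inputs (protocol article, Sample Size):** difference 4; SD 22.25; SD range 12.6 to 31.9; printed d = 0.16; power 90%; two-sided 5%; 317 evaluable; dropout 20%; 400 recruited.

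**1. Effect size.** 4/22.25 = 0.1798, which rounds to 0.18. Working back from d = 0.16: 4/0.16 = 25 for the SD, or 0.16 × 22.25 = 3.56 points for the difference. The paragraph gives neither value.

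**2. Origin of the SD.** (12.6 + 31.9)/2 = 44.5/2 = 22.25. The figure called a median equals the midpoint of the quoted range.

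**3. Trying to reproduce 317.** Paired test, normal approximation: n = ((z₀.₉₇₅ + z₀.₉₀)/d)² = ((1.960 + 1.282)/d)² = 10.507/d².

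- d = 0.16: 10.507/0.0256 = 410.4, so 411. The exact noncentral-t calculation gives 413, about 30% above 317.
- d = 0.1798: 10.507/0.03232 = 325.1, so 326. The exact calculation gives 328, which is 11 above 317.

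The closest a paired test at d = 0.16 comes is 309 (exact), and that needs 80% power, which contradicts the stated 90%. At 90% power, 317 corresponds to d ≈ 0.182, or 0.182 × 22.25 ≈ 4.05 points.

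**4. Power with the planned numbers.** Completers expected: 400 × 0.8 = 320. Exact paired t test, two-sided 5%:

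| Completers | d = 0.16 | d = 4/22.25 |
|---|---|---|
| 317 | 81.1% | 89.1% |
| 320 | 81.4% | 89.4% |

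**5. Dropout step.** 317/0.8 = 396.25, so 397, rounded up to 400. This step is correct. For 90% power, recruitment would be 328/0.8 = 410 at d = 0.18, or 413/0.8 = 516.25, so 517, at d = 0.16.

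**6. Type of SD.** If 22.25 is the SD of a score, with equal variance at both visits, then SD of change = 22.25 × √(2(1 − r)). The correlation r is not in the document, so the values below are assumptions.

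| Assumed r | SD of change | d | Power at 320 |
|---|---|---|---|
| 0.3 | 26.3 | 0.152 | 77% |
| 0.5 | 22.25 | 0.180 | 89% |
| 0.7 | 17.2 | 0.232 | 98.5% |

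At r = 0.5 the two SDs coincide, so using 22.25 directly amounts to assuming a correlation of 0.5.

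**The case against.** The strongest reply is that 0.16 is a reporting slip and the design is sound. The text says the study is powered for the MCID, which is 4 points, and at 4/22.25 the power is 89.1% to 89.4%. The difference, SD, alpha, power and N then agree to about one percentage point; only d is clearly out of line. There is also a possible origin for 317. A point-biserial t-test calculation at an effect of 4/22.25, two-sided 5% and 90% power, returns exactly 317 (power 90.04%), whereas at 0.16 it returns 402. The article does not name the routine used, so this is inference, and that routine is not the paired test the design calls for. It does make it more likely that 317 came from about 0.18 and that 80% power was not used.

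Most of this stands, and it limits the point. A reader might infer from the 81% figure that the trial fails to deliver 90% power. The document supports that only on the condition that d = 0.16 was the intended effect. A reader might also infer that the power claim refers to no identifiable comparison. That goes too far: the visit is fixed as the end of the study, 12 months, and only the domain is unnamed. Calling 22.25 a median is a matter of wording. Not stating the type of SD is a gap in the statement and does not show that the trial is underpowered. How many domains and visits are tested is a separate question from this arithmetic.

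The reply does not remove the contradiction itself: 0.18 cannot round to 0.16, and the printed d, N and power are incompatible for a paired test.

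**Conclusion.** The Sample Size paragraph contradicts itself. Its difference and SD give d = 0.18, the printed d is 0.16, and at the printed d, 90% power and two-sided 5% a paired test needs about 413 completers, not 317.

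The size depends on which input is right. On the protocol's own 4/22.25, the requirement is 326 to 328 and power with 317 to 320 completers is about 89%, a shortfall of about one point. If d = 0.16 was meant, power is about 81%. An unconditional statement that 90% power is not delivered is not supported.

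Both figures rest on a two-sided 5% paired t test with 20% dropout. The 89% also requires 22.25 to be the SD of within-patient change, which equals a pre-post correlation of 0.5 if it is a score SD.

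**What to change.** Keep 400 patients and amend the paragraph:

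1. Correct d to 0.18. If 0.16 was intended, justify it and state that power is about 81% with 320 completers.
2. Restate the claim along these lines: with 320 completers, power is about 89% for a 4-point change from baseline to 12 months, if the SD of change is 22.25.
3. Say that 22.25 is the midpoint of the quoted SD range and is assumed to be the SD of within-patient change; if it is a score SD, say that a pre-post correlation of 0.5 is implied.
4. Name the EPIC-26 domain the statement refers to.

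The cost is wording only. The stated power drops from 90% to about 89% and recruitment is unchanged, provided 4 points and 22.25 remain the planning values. If 0.16 is kept as the target, the cost is a stated power of about 81%.

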### Data Analysis

#### Qualitative Interview Data

The audio recordings for all 30 interviews will be transcribed verbatim. Two members of our research team, (ie, a researcher and research analyst) will first separately code data from 3 patient and 3 caregiver interviews, and record insights and reflections from the data. A conventional qualitative content analysis approach will be used to code qualitative data [62]. Specifically, both researcher and analyst will read through the first interview transcript from beginning to end, similar to reading a novel. Then, they will reread and sort the transcript to identify similar phases, patterns, themes, sequences, and additional important features [63]. These words will become preliminary codes and organized into a coding scheme for use on the remaining 2 interviews. The researcher and analyst together will compare codes and either combine or add new codes. These generalizations will be examined in light of existing knowledge, and representative descriptive texts will be generated. These texts will inform a study codebook, which will then be used to code the remaining 17 patient and 7 caregiver interviews. This codebook will also inform the content analysis process, where descriptive texts will be divided into appropriate thematic categories [64]. We will use the case study analytic techniques of pattern matching and explanation building to build a valid realist program theory [59]. All interview transcripts will be analyzed and coded using NVivo version 11 (QSR International).

#### Quantitative Survey Data

Descriptive statistics will first be conducted on all variables to identify methodological data trends and parameters. We will analyze differences in baseline demographic and clinical variables using Pearson chi-square and nonparametric Wilcoxon rank sum tests. Given that we will be asking the same patients to complete repeated outcome measures across 4 time periods, we will account for autocorrelation effects through the use of linear generalized estimating equations, which are a multivariate analog of linear regression for longitudinal data and recommended for use in longitudinal repeated-measures data analyses [65,66]. Our data analysis strategy to answer the following questions is as follows:

(1) What is the effect of Ned on health-related outcomes over time? To assess the effect of Ned on quality of life, satisfaction with cancer care, unmet needs, self-efficacy, and prostate cancer-related level of anxiety domains, we will use generalized estimating equation models containing indicators for each study time point to assess whether the average study assessment scores at 2 months, 6 months, and 12 months were significantly different from baseline values.

(2) Is there a relationship between patient engagement with Ned and changes in health-related outcomes over time? We will explore whether patients who engage with the content and functionality of the app experience improvements in their health and well-being by building linear regression models for use and outcomes data.

(3) Is there a relationship between health-related outcomes? To understand whether changes in health-related outcomes share a similar direction and magnitude, we will perform Pearson correlation analyses to test for a correlational relationship between outcome variables.

(4) Do demographic and clinical variables affect changes in health-related outcomes? We will first conduct independent *t* tests and 1-way independent analyses of variance to determine whether there were differences in health-related outcomes for all categorical demographic and clinical variables, and Pearson correlation analyses for all continuous variables. We will then perform multiple linear regression analyses with health-related outcomes as dependent variables and all significant predictor variables from our preliminary analyses as independent variables.

We will triangulate both quantitative and qualitative data to develop the realist context-mechanism-outcome pattern configurations required to generate a program theory that explains how Ned is experienced by patients, caregivers, and clinicians.

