### Intervention

The Ned app facilitates prostate cancer survivorship self-care and ownership of personal health data, and enables survivors to share their care plan with their caregiver and clinician to streamline care. Once patients complete the initial download of the Ned app and create an account, they are able to access all of Ned’s features. Patients can check their PSA values from directly within the app once their clinician has approved and released them. All values are first sent from OLIS to the clinician on their version of the Ned app. The clinician must review and approve these values by physically clicking on a button that confirms their attestation to the validity and appropriateness of the value. Only after the clinician has approved and released the PSA value to their patient does it get sent to the patient, who can then view it on their version of the Ned app.

Patients will have scheduled monthly PROMs, specifically the Expanded Prostate Cancer Index Composite (EPIC-26) [39] and the Functional Assessment of Cancer Therapy-Prostate [40], to measure their prostate cancer-specific quality of life. Patients will be prompted to complete these PROMs in-app and submit them directly to be viewed by their clinician on the Ned clinician dashboard. Ned will provide immediate feedback to patients on their health and well-being status with the submission of every PROM.

The app also provides patients with access to Ned’s Notes, a curated feed of educational content coupled with upcoming local social events related to prostate cancer survivorship care. Patients are able to add caregivers to their account; when granted access, caregivers can complete PROMs on behalf of the patient, view PSA results, and take freehand notes on observable health concerns. The centralized hosting of laboratory and PROMs data enables both patients and clinicians to have access to shared data, in the hopes of fostering greater informed decision making. The Ned clinician app and dashboard will provide clinicians with a list of alerts, both for out-of-range PSA and for PROM values. Clinicians can drill down into individual patient profiles and view their PSA values over time. They are also able to view all submitted PROM values and are alerted to outlier trends that require clinical intervention. Figure 2 presents (a) the graphical view of PSA results; (b) Ned’s Notes; and (c) the EPIC-26 survey.

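### GEE with no stated weighting or working correlation, in a one-group pre-post study expecting 20% drop-out, risks a biased 12-month change if leaving depends on earlier scores

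*Protocol article*

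**What the plan says.** In the protocol article, Data Analysis, Quantitative Survey Data, the repeated outcomes are handled as follows: "we will account for autocorrelation effects through the use of linear generalized estimating equations". Question (1), which asks for Ned's effect on all five outcome areas, uses "generalized estimating equation models containing indicators for each study time point". Each of the three follow-up means is thereby tested against the baseline mean. The reason given for GEE is the correlation between repeated measurements. No working correlation, weighting, imputation or missing-data assumption is named.

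The Sample Size section is built on a "minimal clinically important difference (MCID) of 4 with a standard deviation of 22.25 on the EPIC-26" and then allows for loss: "We anticipate a dropout rate of 20%, bringing our total sample size to 400 prostate cancer survivors for recruitment". That inflation is the only use the article makes of the expected drop-out. The design is a single group compared with its own baseline (Trial Design).

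The Intervention section adds a data source that could help with missing assessments: "Patients will have scheduled monthly PROMs", one of which is the EPIC-26. These are completed in the app, separately from the web questionnaires at 0, 2, 6 and 12 months in Table 2.

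**The concern.** Inflating 317 to 400 restores precision but does nothing about who is lost. Ordinary GEE uses whatever scores are present at each visit. It is guaranteed to recover the visit means of the enrolled group only when drop-out is unrelated to the outcome. If men with lower scores tend to leave, the later means come from a healthier remainder. How far GEE corrects for that depends on how much its working correlation borrows from the leavers' earlier scores. Under independence it borrows nothing.

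In a two-arm trial, similar selective loss in both arms would partly cancel. Here the contrast is follow-up minus baseline in one group, so the whole shift would be read as an effect of Ned. The same model serves every outcome area, so the exposure is not confined to the EPIC-26.

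**Working it through.** **Inputs from the article.** SD 22.25; minimal important difference 4; drop-out 20%; 400 recruited; visits at 0, 2, 6 and 12 months; two-sided 5%.

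**The plan's own figures first.**
- 4/22.25 = 0.180. A paired t-test at 90% power then needs 328; 317 gives 89.1%.
- The article instead states "an effect size of Cohen *d*=0.16", which would need 413. This is a separate discrepancy and does not bear on the present point.
- 317/(1 − 0.20) = 396.25, so 400 is a fair rounding up. 400 × 0.80 = 320 men are expected at 12 months.

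**A yardstick.** With SD 22.25 at each visit and a correlation of 0.5 between baseline and 12 months, the variance of the difference in means under independence GEE is 22.25² × (1/320 + 1/400 − 2 × 0.5/400) = 22.25²/320. The standard error is therefore 22.25/√320 = 1.24.

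**Assumptions (not in the article).** Four true correlation structures over the four visits: exchangeable 0.5 and 0.7, AR(1) 0.7 and 0.85. Drop-out is monotone, reaches 20% by 12 months, and its odds are multiplied by 1, 1.5, 2 or 3 per SD lower score. Under MAR the score is the last one observed. Under MNAR it is the next, unseen one. The simulated sample is 400,000, so results are large-sample bias with little noise.

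**Bias in the 12-month change, in points (range over the structures that apply):**

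| Estimator | OR 1 | MAR, OR 1.5 | MAR, OR 2 | MAR, OR 3 |
|---|---|---|---|---|
| GEE, independence | about 0 | +0.95 to +1.39 | +1.56 to +2.27 | +2.30 to +3.28 |
| GEE, AR(1) when truth is exchangeable | about 0 | about +0.4 | about +0.7 | about +1.1 |
| GEE, exchangeable when truth is AR(1) | about 0 | −0.10 to −0.15 | −0.14 to −0.25 | −0.15 to −0.26 |
| GEE, correct or unstructured | about 0 | at most 0.02 | at most 0.08 | at most 0.24 |
| Likelihood model, unstructured | about 0 | at most 0.02 | at most 0.02 | at most 0.02 |

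**Against the study's scale.** At odds ratio 2, independence GEE is off by 1.56/4 = 39% to 2.27/4 = 57% of the minimal important difference. In the exchangeable 0.5 case, where the standard error of 1.24 applies, 1.56/1.24 = 1.25 standard errors. With no true change, a two-sided 5% test would then reject with probability Φ(−1.96 + 1.25) + Φ(−1.96 − 1.25), about 24%.

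**Direction.** If men with higher scores are the ones who leave (odds halved per SD lower), the independence bias reverses to about −1.6 to −2.3.

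**MNAR, odds ratio 2.** The likelihood model is off by +0.78 to +1.21 and unstructured GEE by +0.82 to +1.23. Independence GEE is off by +2.08 to +2.66.

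**The case against.** GEE with visit indicators is a standard method for repeated measures, the article supports it with citations, and its inference does not need normal errors, which suits scores bounded at 0 and 100. Working correlation and missing-data handling are details that an article may leave to a fuller document. The size of the problem turns on exactly those settings, and the largest figures come from one option, independence, which the article does not name. The drop-out mechanism is also assumed. Study assessments are separate from the in-app questionnaires and are compensated individually, so disliking Ned need not mean missing them.

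Much of this stands, and it limits the point. A reader might infer four stronger things that the article does not support:
- That the 12-month change is biased whenever drop-out relates to earlier scores. With a well-fitting or unstructured working correlation the bias is small.
- That the GEE is declared unweighted. That is only read from silence.
- That a mixed model removes the problem. It does so under MAR, with an adequate covariance model; under MNAR it keeps about the same bias as unstructured GEE.
- That the planned baseline chi-square and rank sum tests have no groups to compare. The section on effectiveness lists six treatment groups.

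What the objection does not remove is that the estimator is a stated choice, justified only by autocorrelation, and its validity under score-dependent drop-out hangs on a setting the article does not name. An alternative on the same data does not carry that dependence.

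**Conclusion.** The point holds as a conditional risk that should be closed before analysis. It does not show that the planned estimate is wrong. With 20% drop-out that depends on earlier scores (odds ratio 1.5 to 3 per SD), the bias in the 12-month change runs from close to zero to about 3.3 points, depending on the working correlation. The difference the study is sized to detect is 4 points. If drop-out is unrelated to scores, there is no bias under any of these methods. The odds ratios, the direction of selection and the between-visit correlations are assumptions, since the article gives no figures for them.

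**What to change.** For question (1), replace GEE by a likelihood-based mixed model for repeated measures. It should have categorical visit, unstructured within-patient covariance, every patient with a baseline score, and the same three contrasts (2, 6 and 12 months against baseline). Robust standard errors may be used if wished.

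If GEE is preferred, state an unstructured working correlation and combine it with inverse-probability weighting or multiple imputation. The predictors are already collected: baseline variables, app log data and the monthly in-app EPIC-26. Caregivers may complete in-app questionnaires for the patient, so patient-submitted entries should be used where they can be told apart.

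Either route relies on MAR. Add one delta-adjusted sensitivity analysis that shifts the unobserved scores of men who left and reports how large the shift must be to change the conclusion. A baseline comparison of 12-month completers with non-completers may be added as a separate description.

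The cost is analysis wording only, with no new data or visits. The mixed model makes a slightly stronger modelling assumption (normal errors), which is minor with about 320 to 400 patients.
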